### **Objectives**

To conduct a RCT on the effect of Schroth exercises for AIS compared to the current treatment standard (observation or bracing prescribed as per SRS guidelines). Specific objectives are to compare the effects of 6-month of Schroth exercises added to standard care to standard care alone on curve severity measured using the Cobb angle, and on secondary outcomes including quality-of-life, spinal appearance, objective posture and spinal muscle endurance measurements. We will also compare the effect of 6 months of Schroth therapy offered to control participants after completing 6 months in the standard care group and determine if effects can be maintained until maturity once supervision is terminated.

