#### Schroth exercises:

Patients for which the SRS guidelines would recommend observation as standard of care will do exercises alone. Patients for which the SRS guidelines would recommend bracing will do exercises in addition to being prescribed a brace.

*Private sessions-* During the first 2 weeks, patients will attend 5 1-hour-long individual sessions to learn Schroth principles, exercises and correct breathing, and to confirm independent adequate performance with a checklist.

*Home exercises-* A 30-min. daily home exercise program of 3 to 4 exercises will be adjusted during the first 6 months using an algorithm. Compliance will be monitored using a logbook for 6 months. Completion exercises during the last 12 months will also be monitored using a logbook.

*Group Sessions-* Classes increase compliance. Patients will attend weekly 1-hour-long group therapist-led exercise classes. Adequate

exercise performance will be assessed using the checklist. Pain will be monitored.

*Algorithm* – An algorithm guides exercise prescription, intensity and progression from static to dynamic execution. Prescription begins with easier exercise. If performed adequately, a more challenging exercise will be tried. If performance is inadequate, an easier exercise will be attempted. Exercises performed adequately will be prescribed.

At follow-up, if performance is adequate, dosage will increase to target intensity. Target intensity increases repetitions aimed to enhance endurance. Final tension intensity is nearly maximum isometric contraction held in corrected posture.

During the COVID-19 pandemic, the few participants still receiving exercises will be offered the choice to receive therapy in person or via videoconference. Our therapist [name] has access to a secure videoconferencing system (JaneApp) to deliver this therapy remotely. Alternatively [name] has access to a secure ZOOM space. No recording is made during the videoconferencing session.

Controls: Controls will receive the standard of care appropriate for their curves (observation or bracing prescribed as per SRS guidelines), and will complete baseline, 3 and 6 months exams. After 6 months they will cross-over to the treatment group.

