## **Analyses:**

Intention to treat (by carrying forward last known value) linear mixedmodel analyses will be used to assess differences in group changes from baseline, to 3 and 6-month while adjusting for covariates. Separate analyses will be conducted for each outcome. To screen for variables associated with each of the outcomes variables, we will use univariate linear mixed models and include all relevant covariates (age, time since menarche, apex levels, physical activity, self-efficacy, and bracing compliance may have associations with risk of progression). Multiple linear mixed models will be tested including covariables found significant at  $P=0.20$  in the univariate analysis, and after screening for multicollinearity. Results will be presented as effect sizes with confidence intervals and one-sided P-values. Statistical analyses will be performed using SAS version 9.1.

For subjects initially in the control group later completing 6 months of exercises, intention to treat linear mixed-model analyses will be used to assess differences between the two periods (standard care vs standard care + Schroth) in changes from baseline, to 3 and 6-month, while adjusting for covariates. Screening for covariates will be done as described above. In this model, treatment period is a dependent factor.

To determine if exercises effects are maintained at 12 months and discharge exams, linear mixed- model analyses will also be used to quantify the effect sizes corresponding to changes from 6 to 12 months and to discharge by combining data from all patients after participating in the exercise program.

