## 5.0 Justification for sample size:

Primary and secondary aim 1: A sample of 129 subjects per group will be sufficient to detect a 0.31 effect size when comparing the change in outcomes between the exercise and control groups with 80% power using a unilateral test and an alpha of 0.05 (104 Schroth and 104 controls in this study + 25 Schroth and 25 controls in the pilot allows a total of 129 per group). We anticipate >80% completion rate based on published data and because the pilot dropout rate was <10%. Our per-protocol sample may drop slightly however, we are planning intent to treat analyses where we will carry-forward the last known observation from our participants.

A unilateral hypothesis is justified, for this superiority trial, by positive published data and our pilot data. The pilot effect size for the Cobb angle was 0.32 and many secondary outcomes had effect sizes exceeding what we are powered to detect as significant. A trial conclusive in favour of exercises would have a significant impact in America. A trial failing to demonstrate positive results would have less impact as Schroth exercises are not currently prescribed. We believe that a 0.32 effect size is clinically important, feasible, and would justify implementing a Schroth program. The trial duration is relatively short which justifies aiming to detect a small effect size (0.2-0.5) .

It would be inadequate to power the trial to detect too small an effect size as patients and families will likely demand evidence of clinically important effects before committing efforts and time required of Schroth exercise programs. For the secondary aim comparing the results of subjects in the control group who first complete 6 months as controls to their results after completing 6 months of Schroth exercises, an effect size of 0.27 (n=106) could be detected as significant with a power of 0.80, an alpha of 0.05 with a unilateral test.

ID: Pro00043397

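### The secondary crossover analysis is labelled intention to treat, but its population is defined by completing 6 months of exercise

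*Protocol*

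**What the plan says.** The places are all in the Protocol.

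- **Section 2.1, Objectives.** The aim is to examine the effect of "6 months of Schroth therapy offered to control participants after completing 6 months in the standard care group". The only completion condition concerns the control period.
- **Section 2.1, Schroth exercises, paragraph on controls.** "After 6 months they will cross-over to the treatment group". No condition on finishing the exercises is attached.
- **Section 2.1, Analyses.** The crossover paragraph opens "For subjects initially in the control group later completing 6 months of exercises, intention to treat linear mixed-model analyses" and says these will "assess differences between the two periods (standard care vs standard care + Schroth) in changes from baseline, to 3 and 6-month". Last-value carry-forward is named in the preceding paragraph, for the between-group analysis; the crossover paragraph carries only the intention-to-treat label.
- **Section 4.2, Justification for sample size.** The crossover comparison is of "subjects in the control group who first complete 6 months as controls to their results after completing 6 months of Schroth exercises", and "an effect size of 0.27 (n=106) could be detected as significant with a power of 0.80, an alpha of 0.05 with a unilateral test". The same item expects more than 80% completion and reports pilot dropout under 10%. It also distinguishes a per-protocol sample from intention-to-treat analyses.

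No sentence brings back into this analysis a control who declines the exercises or starts and does not finish them.

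**The concern.** Finishing 6 months of exercise happens after the exercise period has begun. A set defined by it is a completer set, and the intention-to-treat label does not describe it. An analysis plan could follow the population or the label, and would get different patient sets.

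The aim concerns therapy offered to controls. If those who stop differ from those who finish in how they respond while exercising, a completer set estimates something else. Comparing each patient with herself removes stable differences between patients but not selection on what happens during the second period. P-values are one-sided, so any bias towards benefit feeds directly into the false-positive rate for this aim. Carry-forward, if it was meant to apply here, has little left to act on once non-finishers are out.

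**Working it through.** **1. The plan's own figure.** For a paired comparison with standardised effect d, n = ((z_alpha + z_power)/d)².

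- One-sided alpha 0.05, power 0.80, as stated: ((1.645 + 0.842)/0.27)² = 84.8, so 85 patients. With n = 106 the detectable effect is 2.487/√106 = 0.24, and power at 0.27 is 87%. The stated pair does not reproduce.
- Two-sided alpha 0.05: (1.960 + 0.842)/√106 = 0.272, with power 79.4% at 0.27. This reproduces it closely, as does a one-sided test with 80% of 106 (85 patients).

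The mismatch is a separate matter, but it is relevant when n is restated.

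**2. What 106 might be.** This study has 104 controls and the pilot 25, together 129. The figure of 106 exceeds 104, and 106/129 = 82%, close to the expected completion of more than 80%. That is consistent with a count of completers, but the Protocol does not say how 106 was obtained.

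**3. Illustration of the selection effect.** Assumptions not in the Protocol: finishing is a threshold on a normally distributed tendency, and ρ is its correlation with the outcome. If a fraction c finishes, the finishers' mean shifts by ρ × φ(z)/c, where z cuts off the lowest 1 − c.

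- c = 0.80: φ(0.842)/0.80 = 0.280/0.80 = 0.350
- c = 0.90: φ(1.282)/0.90 = 0.1755/0.90 = 0.195

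The result depends on what ρ refers to:

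| What finishing is related to | ρ | c = 0.80 | c = 0.90 |
|---|---|---|---|
| Both periods' change equally (stable trait) | any | 0 | 0 |
| Exercise-period change only | 0.3 | 0.105/√2 = 0.074 | 0.058/√2 = 0.041 |
| The between-period difference | 0.1 | 0.035 | 0.019 |
| The between-period difference | 0.3 | 0.105 | 0.058 |

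Entries are in SD of the between-period difference. The second row also assumes equal variance and no correlation between the two periods' changes, so that the SD of the difference is √2 times that of one period.

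Against the 0.27 used for this aim, the nonzero rows with ρ = 0.3 run from 0.041/0.27 = 15% to 0.105/0.27 = 39%. If there is no true effect and 129 controls cross over, the one-sided type I error is Φ(shift × √n − 1.645). For the last two rows it runs from 8% (ρ = 0.1, c = 0.90, n = 116) to 28% (ρ = 0.3, c = 0.80, n = 103) instead of 5%. For a stable trait it stays at 5%.

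**4. Analysing everyone who crosses over.** At one-sided alpha 0.05 and power 0.80, the detectable effect is 2.487/√129 = 0.22, or 2.487/√104 = 0.24. As an assumed example, let the effect be 0.27 in finishers and 0 in the rest. The overall effect is 0.80 × 0.27 = 0.22 or 0.90 × 0.27 = 0.24. Power is then 79 to 87% with 129 patients and 71 to 80% with 104.

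**The case against.** The strongest reply is that the wording is loose. Completing may mean no more than going through the 6-month exercise period. The same sentence says intention to treat, the Objectives speak of therapy offered, and the sample-size item describes the comparison in time order rather than as a formal analysis set. That reading is possible, so a reader should not infer that the sponsor has certainly decided to exclude non-finishers. But the condition appears in two places, no text overrides it, and the passages still have to be reconciled.

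A second reply is that analysis sets belong in the statistical analysis plan. That would answer a gap. Here the Protocol states both a population and a label, and the two conflict.

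Several stronger readings are tempting and are not supported:

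- **That membership requires the whole programme, or tolerance of it.** The Protocol gives no completion threshold and does not mention tolerance in this context.
- **That a patient prescribed a brace leaves the comparison.** Bracing is part of standard care in both periods, and the Protocol has braced patients exercise as well.
- **That the bias is 39% of the effect of interest and favours exercise.** That figure needs 80% completion and a correlation of 0.3 with the between-period difference itself. Both periods come from the same selected patients, so a stable trait cancels. Pilot dropout was under 10%, and patients could also stop for reasons unrelated or oppositely related to response.

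**Conclusion.** The point stands as a contradiction between population and label in a secondary aim. Followed literally, the stated rule gives a completer analysis. Whether and how far this biases the period contrast cannot be derived from the Protocol. The range of about 0 to 0.1 SD of the between-period difference is illustrative only. It rests on assumed correlations up to 0.3, 80 to 90% completion and a normal threshold model.

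A reader might infer that the trial's main result is compromised. It is not: the primary comparison of randomised groups does not use this set. A reader might also infer that the completer result will be presented as the effect of offering exercise. The label makes that possible, but nothing in the Protocol says so. The change is still worth making, because it removes a possible source of bias at little cost.

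**What to change.** In the Analyses section and the sample-size justification, define the crossover set as all controls who reach the month-6 crossover point, whatever amount of exercise they then do.

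- For Cobb angle and SRS-22, use the 12-month radiograph and questionnaire. Sections 2.1 and 5.1 already have these extracted from clinic records, and clinic visits are routinely every 6 months.
- For outcomes collected only at study visits (endurance, pain, self-efficacy, global rating of change and the 3-month exams), apply the plan's stated missing-data handling, and say explicitly that it covers this analysis.
- Restate the n of 106 for the new set, with its derivation and whether pilot controls are counted. Reconcile it with the one-sided test at the same time.
- Report the completer set only as a labelled per-protocol or supportive analysis.

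The cost is somewhat more than wording. The estimated effect may be smaller, and some study-visit data will be missing in those who stop, since the 3-month exam and several measures are additional to routine visits. The detectable effect for the full set (0.22 with 129 patients, 0.24 with 104) is still below 0.27, but the effect itself may be diluted, with the power shown above.

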#### **4.0 \* Describe how you will manage and minimize risks and discomforts, as well as mitigate harm:**

- We do not expect adverse effects to result from the study. All the procedures are routinely used in the assessment of patients with scoliosis and are considered non-invasive. In the unlikely event where we would detect a spinal deformity or a pathology warranting further investigation, we will provide information on the nature of our findings and suggest referral to the patient's family physicians. We will be available to discuss our findings with the physician at the patient's request. Testing procedure can be interrupted at the patient's request at anytime.

- The surface topography scanning procedures are all done by a female. The subjects will be oriented to the scanning area. Participants will be instructed in the use of the stick-on bras. The evaluator will then leave the patient in the closed off scanning area to disrobe privately and apply the bras. The patient will be given a hospital gown for privacy when the

evaluator returns to apply the reference marks on the skin and to adjust the positioning frame. The evaluator will then leave again and the patient will disrobe. The surface scan will be obtained immediately. During the scan the subject will be offered to be accompanied by a family member or a friend if they desire. The scanner operator will be a female. The analysis of the scan will be done by a female and the head will be cropped off of the scan to protect patient privacy. Patients may refuse to participate at any point.

- Schroth therapist will individually instruct all the patients in the execution of the exercises in the first 5 sessions, and the group sessions will be led by a Schroth therapist. All exercises can be modified to minimize possible discomfort that can be caused by inadequate level of intensity.

- In the case of patient's scoliosis progression to the extent where bracing or surgery prescription criteria are met, they will be referred to their treating surgeon and prescribed treatment deemed appropriate. SRS prescription criteria will be used.

For exams, participants will be invited to complete questionnaires at home to minimize visit duration. All exams will occur in CSB to avoid visiting too many sites which would increase their risk of exposure to COVID 19. The EHS plan for [name] lab requires a clear AHS Covid-19 screen for both patients and therapist.

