## 2.0 **\* Describe and justify the inclusion criteria for participants (e.g. age range, health status, gender, etc.):**

Patients with Adolescent Idiopathic Scoliosis (AIS), with juvenile idiopathic scoliosis (JIS), or syringomyelia without chiari from the Specialized Scoliosis Clinic in Edmonton, Calgary, Montréal (n=208) will be recruited from our scoliosis clinics. AIS is defined as idiopathic scoliosis diagnosed between the ages of 10-16. JIS is defined as idiopathic scoliosis diagnosed between the ages of 5-10. Idiopathic scoliosis may have appeared between the ages of 5-10, but not been diagnosed until after the age of 10. Therefore, including patients with JIS and AIS in the study is not including two distinct forms of scoliosis, rather a continuum of idiopathic scoliosis. Patients with syringomyelia without chiari are common and does not exclude a patient's diagnosis as AIS or JIS.

Only females are targeted. Females are more frequently severely affected to levels justifying a treatment prescription. Other inclusion criteria are:

(1) magnitude of spinal curve 10° to 45° (Cobb angle),  
 -Larger curves meet the clear indication recommended by the Scoliosis Research Society to be prescribed surgery. Small curves in skeletally immature adolescents have higher risk of progression. Curves over 30° are more likely to progress after skeletal maturity. European consensus for conservative treatment recommends exercises alone below 20° and exercises in combination with a brace for patients with curves greater than 20°.

(2) may be treated with or without brace  
 -We have broadened inclusion criteria to be inclusive of all conservative treatment offered at the Specialized scoliosis clinic in Edmonton, Calgary and Montréal (observation and bracing). European consensus for conservative treatment recommends exercises alone below 20° and exercises in combination with a brace for patients with curves greater than 20°. Including patients with and without brace treatment allows for comparison of exercise alone and in combination with brace treatment. Including brace treatment as a potential predictor of treatment success is representative of decisions clinicians are making in the treatment of patients with scoliosis. We will examine whether bracing in combination with exercises is predictive of success beyond the other treatment combinations.

(3) Risser 0-3 (indicating Incomplete skeletal maturity)  

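### The control-group crossover analysis compares months 0–6 with months 6–12 in one fixed order, so it cannot separate Schroth from time; it should be descriptive, not a powered one-sided test

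*Protocol*

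**What the plan says.** The Objectives in Protocol section 2.1 include the effect of six months of Schroth offered to controls after their six months of standard care. Under Schroth exercises, the paragraph on controls fixes the order: "After 6 months they will cross-over to the treatment group". No participant has the reverse order.

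The second paragraph of Analyses says that, for these participants, mixed models "will be used to assess differences between the two periods (standard care vs standard care + Schroth"). The sentence goes on: "in changes from baseline, to 3 and 6-month, while adjusting for covariates. Screening for covariates will be done as described above". The candidates named for screening are "age, time since menarche, apex levels, physical activity, self-efficacy, and bracing compliance may have associations with risk of progression". They enter the multiple model only if significant at P=0.20 in the univariate model and after a multicollinearity screen. The paragraph ends: "In this model, treatment period is a dependent factor". It mentions neither the Schroth arm nor a separate term for time.

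Section 4.2, item 5.0 (Justification for sample size) gives the contrast its own power statement, beginning "For the secondary aim comparing the results of subjects in the control group who first complete 6 months as controls to their results". It claims that an effect size of 0.27 is detectable with n=106, power 0.80 and a one-sided alpha of 0.05.

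**The concern.** In a crossover with two sequences, the reverse sequence estimates the period effect. Here there is one sequence, so period and treatment are the same variable.

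The protocol itself gives reasons to expect the periods to differ. On maturity, section 4.2 says: "Small curves in skeletally immature adolescents have higher risk of progression". Each girl is about six months older in the second period. On co-treatment, section 3.1, item 4.0 provides for a change of care: "In the case of patient's scoliosis progression to the extent where bracing or surgery prescription criteria are met", the participant is referred to the treating surgeon. Regression to the mean after enrolment at a clinic visit is a third possibility.

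At stake is a stated objective, tested one-sided. If progression slows for any of these reasons, the test can show a significant benefit when Schroth does nothing.

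**Working it through.** **1. The plan's own figure.** Paired normal approximation: n = ((z₀.₉₅ + z₀.₈₀)/d)² = ((1.645 + 0.842)/0.27)² = 84.8, so 85 pairs. Since 106 × 0.80 = 84.8, the stated n=106 fits the one-sided test if about 20% non-completion is built in. With all 106 analysed, power at 0.27 would be 0.87 and the detectable effect 2.487/√106 = 0.24. The figure reproduces. The difficulty lies in what the test estimates.

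**2. What the contrast estimates.** Let Y₁ and Y₂ be a control's six-month change in each period, α the patient's own level, X a baseline covariate, δ the period effect and τ the Schroth effect:

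- Y₁ = α + γX + error
- Y₂ = α + γX + δ + τ + error
- mean of (Y₂ − Y₁) = δ + τ

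The baseline term cancels, so adjusting for it leaves δ + τ unchanged. Any drift δ enters the Schroth estimate degree for degree.

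**3. Does the listed adjustment help?** Simulation with no Schroth effect, n=106, ages uniform from 10 to 16, progression falling linearly with age (all but n and the age limits are assumptions), 4,000 runs. Drift is in SDs of the within-patient difference; entries are one-sided rejection rates against a nominal 5%.

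| Drift | Unadjusted | Baseline age | Age updated each period |
|---|---|---|---|
| 0 | 4.9% | 4.7% | 4.8% |
| 0.10 | 26.3% | 26.5% | 4.6% |
| 0.20 | 66.0% | 66.4% | 5.4% |

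Baseline age does nothing. Updated age works here because the simulated model is exactly linear in age. The protocol does not say which version is meant.

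**4. Size in degrees.** From the protocol: 104 controls, one-sided 0.05. Assumed: SD of six-month Cobb change 4–6 degrees, correlation ρ of successive changes 0 to −0.3 (negative because the 6-month film ends one change and starts the next), τ = 0, no effective adjustment.

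- SD of the difference = SD × √(2(1 − ρ)): 4 × √2 = 5.66 at the low end, 6 × √2.6 = 9.67 at the high end.
- Noncentrality = δ × √104 / SD of the difference, referred to a noncentral t on 103 df.

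| Slowing δ | SD of difference 9.67 | SD of difference 5.66 |
|---|---|---|
| 0.5 degrees | noncentrality 0.53, rejects 13% | 0.90, rejects 23% |
| 1.0 degree | 1.05, rejects 28% | 1.80, rejects 56% |

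If progression quickened by the same amounts, the rejection rate would be 1.5% or less and a real benefit would be understated by the same number of degrees.

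**The case against.** The best reply is that the analysis is covariate-adjusted, and that age, time since menarche and bracing compliance are the variables one would choose against maturation and brace changes. Nothing in the Analyses text freezes them at enrolment; the statement in Procedures that predictors are collected at baseline concerns predictors of success. Covariate timing could also sit in a statistical analysis plan that is not at hand. This stands in part. A reader might infer that the plan credits the whole period difference to Schroth without adjustment, and it does not. But the covariates must survive two screens and are not stated to be period-specific. Updated age is itself tied to period, and brace changes may respond to progression. Adjustment is partial at best, and the protocol already fixes the one-sided, powered contrast.

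A second reply is that the direction of drift is unknown. This stands. A reader might infer that progression must slow, or that brace starts can only accumulate. Eligibility spans ages 10–16 and Risser 0–3, the documents give no six-month rate by period, and nothing excludes a brace being stopped or worn less.

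Third, "In this model, treatment period is a dependent factor" may simply mean a dependent-samples, within-patient factor. That is a fair reading; the wording is loose rather than proof of a wrong model.

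Fourth, a two-arm model using the Schroth arm's months 6–12 as the period control has weaknesses of its own. That arm has already had Schroth, logbooks continue, and assuming no carry-over sits badly with the objective on maintained effects. Only radiographs and SRS-22 are scheduled at 12 months. This stands against making that model the replacement.

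**Conclusion.** The concern holds in limited form. Treatment and period are fully aliased in the control-only contrast, and the planned adjustment cannot be relied on to separate them. Under the assumptions in the working, slowing of 0.5–1.0 degrees gives a false-positive rate of about 13–56% against a nominal 5%. That range is conditional on assumed drift, SD and correlation and on adjustment achieving nothing; it is not the error rate of the planned model.

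Two stronger conclusions are tempting and not supported. One is that the trial's main result is compromised: the randomised 0–6 month comparison does not use the second period and is unaffected. The other is that the crossover result would be offered as a second confirmation of efficacy: the protocol calls it a secondary aim and says nothing of the kind. This is a should-fix point.

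**What to change.** In Protocol section 2.1 (Analyses, second paragraph) and section 4.2, item 5.0:

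- Report the control-group period contrast as a descriptive before/after estimate with a confidence interval. Remove the one-sided P-value, the power claim and the attribution to Schroth.
- State that period is confounded with treatment.
- Use age, time since menarche and bracing status measured at the start of, or during, each period.
- Call treatment period a within-patient explanatory factor.

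Optionally, for Cobb angle and SRS-22 only, add as a sensitivity analysis a mixed model on both randomised arms at 0, 6 and 12 months with a period term. State that it assumes no carry-over in the Schroth arm after month 6 (a lasting benefit makes it conservative, a rebound too favourable) and that it contains the primary comparison, so it is not independent evidence.

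The change to the main report is mostly wording; the covariates need a value for the second period. The price is the stand-alone efficacy claim from the crossover.
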